# ProFertil study protocol for the investigation of gonadotropin-releasing hormone agonists (GnRHa) during chemotherapy aiming at fertility protection of young women and teenagers with cancer in Sweden—a phase III randomised double-blinded placebo-controlled study

**DOI:** 10.1136/bmjopen-2023-078023

**Published:** 2023-12-08

**Keywords:** gynaecological oncology, oncology, reproductive medicine, subfertility, chemotherapy

## Abstract

**Background:**

Gonadotropin-releasing hormone agonists (GnRHa) cotreatment used to transiently suppress ovarian function during chemotherapy to prevent ovarian damage and preserve female fertility is used globally but efficacy is debated. Most clinical studies investigating a beneficial effect of GnRHa cotreatment on ovarian function have been small, retrospective and uncontrolled. Unblinded randomised studies on women with breast cancer have suggested a beneficial effect, but results are mixed with lack of evidence of improvement in markers of ovarian reserve. Unblinded randomised studies of women with lymphoma have not shown any benefit regarding fertility markers after long-term follow-up and no placebo-controlled study has been conducted so far. The aim of this study is to investigate if administration of GnRHa during cancer treatment can preserve fertility in young female cancer patients in a double-blind, placebo-controlled clinical trial.

**Methods and analysis:**

A prospective, randomised, double-blinded, placebo-controlled, phase III study including 300 subjects with breast cancer. In addition, 200 subjects with lymphoma, acute leukemias and sarcomas will be recruited. Women aged 14–42 will be randomised 1:1 to treatment with GnRHa (triptorelin) or placebo for the duration of their gonadotoxic chemotherapy. Follow-up until 5 years from end of treatment (EoT). The primary endpoint will be change in anti-Müllerian hormone (AMH) recovery at follow-up 12 months after EoT, relative to AMH levels at EoT, comparing the GnRHa group and the placebo group in women with breast cancer.

**Ethics and dissemination:**

This study is designed in accordance with the principles of Good Clinical Practice (ICH-GCP E6 (R2)), local regulations (ie, European Directive 2001/20/EC) and the ethical principles of the Declaration of Helsinki. Within 6 months of study completion, the results will be analysed and the study results shall be reported in the EudraCT database.

**Study registration:**

The National Institutional review board in Sweden dnr:2021–03379, approval date 12 October 2021 (approved amendments 12 June 2022, dnr:2022-02924-02 and 13 December 2022, dnr:2022-05565-02). The Swedish Medical Product Agency 19 January 2022, Dnr:5.1-2021-98927 (approved amendment 4 February 2022). Manufacturing authorisation for authorised medicinal products approved 6 December 2021, Dnr:6.2.1-2020-079580. Stockholm Medical Biobank approved 22 June 2022, RBC dnr:202 253.

**Trial registration number:**

NCT05328258; EudraCT number:2020-004780-71.

Strengths and limitations of this studyDouble-blinded randomised placebo-controlled study.The study will recruit both teenagers and young women to cover the full span of female fertility.The study will include several common cancer diagnoses among young females.The study is underpowered to detect diagnosis-specific differences outside the subcohort with breast cancer.The study has a long follow-up and might suffer from higher than estimated drop-out rates.

## Introduction

### Ovarian protection

The utilisation of gonadotropin-releasing hormone agonists (GnRHa) as a means to protect the ovaries from chemotherapy^1^ is becoming increasingly common worldwide, even in subjects undergoing less gonadotoxic chemotherapeutic treatments, such as those indicated for benign diseases. But the effect of a GnRHa co-treatment and the mechanism for transient suppression of the ovarian function during chemotherapy are still under debate.^2–5^

The primary mechanism proposed for GnRHa-mediated protection of the ovarian reserve involves keeping the primordial follicles dormant throughout chemotherapy by antagonistic occupation of the GnRH receptor, leading to desensitisation of the pituitary gland and suppression of follicle stimulating hormone (FSH) and luteinising hormone (LH) secretion, with a profound hypogonadal effect achieved through receptor downregulation by internalisation of receptors. But primordial follicles are non-proliferating, and not regulated by gonadotropins as they lack both FSH and GnRH receptors.^6^ Thus, administration of GnRHa should not be able to block their initial recruitment towards maturation, at least not through the proposed mechanism.^2–5^ If GnRHa has an antagonistic effect on the ovarian cytotoxicity of chemotherapeutics, as has been suggested, systemic use of GnRHa would likely reduce the overall effect of chemotherapy, which does not seem to be the case.^7 8^ Nevertheless, it is possible that prophylactic GnRHa therapy acts through mechanisms yet unknown. A recent scientific debate article has highlighted the inconsistencies among research publications,^5^ and the American Society of Clinical Oncology (ASCO)’s expert panel did not recommend ovarian suppression using GnRHa as a method for fertility preservation in its updated guidelines for fertility preservation for patients with cancer published in July 2018.^7^ However, several medical societies, such as the European Society for Medical Oncology (ESMO)^8^ are currently advocating its utilisation, alone or in combination with fertility-preservation strategies for breast cancer patients treated with (neo)adjuvant chemotherapy.^8^ In many countries, the GnRHa treatment is offered because of its relatively low cost in comparison to the higher expenses surrounding proven methods for fertility preservation, such as gonadotropin stimulation treatment aimed at cryopreservation of eggs or embryos or the surgical retrieval of ovarian tissue for cryopreservation.^7^

### Clinical studies on the protective effect of GnRHa

Most clinical studies supporting a beneficial effect of GnRHa cotreatment on ovarian function have been small, mainly retrospective and uncontrolled, and have used resumption of menses as surrogate to ovarian function after chemotherapy.^5^ There are randomised studies of GnRHa cotreatment during chemotherapy in women with cancer, most of small size.^9–22^ Importantly, as all available studies have been unblinded, the women who received GnRHa have known that the drug was administered to protect their fertility potential. This potential bias has been discussed in the literature, as the women who received GnRHa also reported higher frequency of pregnancy attempts.^2 11^

Serum AMH concentration is currently considered the gold standard marker of ovarian reserve^23–25^ and since 2010 it has been included as an outcome measure in some of the randomised studies available on GnRHa cotreatment.^16–22^ None of the studies investigating changes in ovarian markers following chemotherapy have found a beneficial effect of GnRHa cotreatment on AMH recovery.^16–22^ Results from available randomised controlled studies that assessed markers of ovarian reserve are shown in table 1.

**Table 1 T1:** Data on biochemical markers of ovarian reserve from randomised controlled studies investigating GnRHa cotreatment during gonadotoxic treatment in women with cancer

Type of cancer	Author, year	Ovarian marker studied	Protective effect (yes/no)	Study results
Hodgkin lymphoma	Nitzschke *et al*, 2010^22^	AMH and inhibin	No	Follow-up 2.7 years. No difference between the groups.
Hodgkin lymphoma	Behringer *et al,* 2010^17^	AMH and inhibin	No	Follow-up 18 months. Ovarian markers reduced in both arms.
Breast cancer	Munster *et al,* 2010^21^	Inhibin	No	Follow-up 18 months. Two pregnancies in the control group.
Breast cancer	Gerber *et al*, 2011^20^	AMH and inhibin	No	Follow-up 6 months. Ovarian markers reduced in both arms.
Breast cancer	Elgindy *et al*, 2011^19^	AMH	No	Follow-up 12 months. Ovarian marker reduced in both groups.
Breast cancer	Del Mastro *et al*, 2011^10^	No sensitive ovarian markers investigated. FSH randomly assessed	Yes	Follow up 12 months. Menstruation resumption reported but subjectively in an unblinded study.
Breast cancer	Moore *et al*, 2015 and 2019 11 12	No sensitive ovarian markers investigated, FSH and inhibin measured but results not reported	Yes	Study originally powered for 416 patients. Number reported by ITT 218 with only 135 with complete data after 2 years follow up. Menstruation resumption reported but in an unblinded study. Women attempted and achieved pregnancy to a higher degree in the group that received GnRHa.
Breast cancer	Leonard *et al,* 2017^16^	AMH and FSH	Yes	Follow up 24 months. Significant reduction of amenorrhoea. No significant difference in AMH.
Lymphoma	*Demeestere et al, 2016* 18	AMH and inhibin	No	Follow-up 7 years. No effect on AMH or in pregnancies.

AMH, anti-Müllerian hormone; FSH, follicle stimulating hormone; GnRHa, gonadotropin-releasing hormone agonists; ITT, intention-to-treat.

### Study rationale

Among all sequelae of cancer treatment, infertility is recognised to have a high negative impact on quality of life in cancer survivors. If GnRHa treatment can be associated with maintained fertility, it would be particularly suitable for the young subjects, or for subjects that require immediate cancer therapy and do not have the opportunity to perform established and time-demanding fertility preservation procedures. However, if the GnRHa treatment does not show any protective effects, available resources should be devoted to established methods of fertility preservation and research should focus on finding new therapies that can prevent infertility in our youngest cancer patients.

The bulk of data on GnRHa cotreatment in women receiving chemotherapy for treatment of cancer is originated from two specific patient groups, those of women with breast cancer and lymphoma (Hodgkin’s lymphoma and non-Hodgkin’s lymphoma), as summarised in table 1. We aim to estimate the changes in ovarian reserve following chemotherapy for treatment of cancer with or without GnRHa by determination of the AMH at 12 months after end of gonadotoxic treatment (EoT) in women with breast cancer, but the study will also include subjects receiving less gonadotoxic treatment, such as the primary treatment of acute leukaemia, as well as subjects receiving very high gonadotoxic treatment, such as treatment of sarcoma, both diseases with a high incidence among teenagers. As none of the available randomised studies has been blinded or placebo controlled so far, and none has previously included young teenagers, our clinical trial is underpinned by a good medical and scientific rationale. The debate on the effect of ovarian protection using GnRHa or other means of gonadotropin suppression has lasted since the mechanism was hypothesised over 40 years ago^1^ and our aim is to employ modern biochemical markers of ovarian reserve to investigate if the administration of GnRHa during cancer treatment can preserve the fertility of young female cancer subjects.

Here we report a summary of our protocol for a prospective phase III study, randomised, double-blinded, placebo-controlled, that adhere to International Council for Harmonisation-Good Clinical Practice (ICH-GCP) and Standard Protocol Items: Recommendations for Interventional Trials (SPIRIT) guidelines. V.2.5 2022-09-27 of the protocol is available as online supplemental material 1 and any substantial amendments will be available on clinicaltrials.gov or by request from the corresponding author. The SPIRIT checklist refers to the full protocol.

10.1136/bmjopen-2023-078023.supp1Supplementary data

## Methods and analyses

### Hypothesis and aim

We hypothesise that if GnRHa has a protective effect on the ovarian reserve when given during chemotherapy, this effect will be reflected in effect measurements of biochemical markers of fertility such as AMH, FSH, LH, inhibin, estadiol and clinically measured outcomes such as antral follicle counts (AFC) on transvaginal ultrasonography and resumption of menses. Our primary objective is to estimate the changes in ovarian reserve markers following chemotherapy for treatment of cancer with or without GnRHa by determination of the AMH at 12 months after end of gonadotoxic treatment (EoT) in women with breast cancer. A full list of the study objectives are listed in table 2.

**Table 2 T2:** Primary and secondary objectives

Primary objective	
	To estimate the changes in ovarian reserve following chemotherapy for treatment of cancer with or without GnRHa by determination of the anti-Müllerian hormone (AMH) at 12 months after end of gonadotoxic treatment (EoT) in women with breast cancer.
Secondary objectives	
Key secondary objective	To estimate the changes in ovarian reserve following chemotherapy for treatment of cancer with or without GnRHa by determination of the AMH at 12 months after EoT in women with acute leukemias, lymphomas and sarcomas.
Secondary objectives (to be evaluated at EoT, 6, 12 months after EoT and continuously during follow-up years 2, 3, 4, 5 after EoT)	To estimate the changes in ovarian reserve with or without GnRHa by determination of the antral follicle counts (AFC) in women with breast cancer.
	To estimate the changes in ovarian reserve with or without GnRHa by determination of the AFC in women with acute leukemias, lymphomas and sarcomas.
	To estimate the changes in ovarian reserve with or without GnRHa by longitudinal observation of AMH levels in women with breast cancer.
	To estimate the changes in ovarian reserve with or without GnRHa by longitudinal observation of AMH levels in women with acute leukemias, lymphomas and sarcomas.
	To compare the proportion of females with or without GnRHa that develops ovarian insufficiency by determination of follicle stimulating hormone (FSH), inhibin and estradiol at standardised timepoints.
	To investigate the impact of body mass index (BMI), use of contraceptives and endocrine adjuvant therapy in changes of ovarian reserve with or without GnRHa by longitudinal observation of AMH levels, FSH, inhibin and estradiol at standardised timepoints.
	To investigate the effect of GnRHa on ovarian blood supply.
	To estimate the proportion of females with or without GnRHa that develop amenorrhoea (no menstruations).
	To investigate fertility and childbirth after cancer treatment in women with or without GnRHa who attempt pregnancy during follow-up.
	To determine health-related quality of life (QoL) with or without GnRHa during chemotherapy and after cancer treatment.
	To study development of comorbidities during follow-up and bone mineral density after completion of cancer treatment with or without GnRHa.
	To estimate disease-specific oncologic outcomes, recurrence rate, overall survival and disease-free survival with or without GnRHa.

GnRHa, gonadotropin-releasing hormone agonists.

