### Blinding

All personnel involved in the study, sponsor, investigators, site staffs and monitors, statisticians and subjects, except personnel preparing triptorelin/placebo at the local site and an unblinded monitor, will be blinded during the study. An unblinded research nurse at each site will prepare blinded triptorelin/placebo to subjects and manage registration in the web-based randomisation system ALEA, used to allocate blinded triptorelin/placebo to subjects at randomisation.

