### Sample size calculation and statistical analyses

The sample size calculation was done assuming a mean difference in log10-transformed AMH-levels of 0.22 between GnRHa group and placebo group (with a ratio 1:1). It was further assumed that data are approximately normally distributed, and that each treatment group has a SD of 0.63.^26^ Under these assumptions, the hypothesis test (a two-sided test with significance level 5%) of the mean effect between GnRHa group versus placebo group will have a power of at least 80% if the sample size is 300 (including an assumed 15% drop-out rate).

Primary and secondary endpoints will be evaluated using the intention-to-treat (ITT) (ie, all randomised subjects), the per protocol (PP) analysis set (ie, all randomised subjects with no major protocol violations) and the safety analysis set (all subjects) (figure 2). The classification of each subject with respect to each analysis set will be done prior to database lock.

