### Data analysis plan

An interim report will be produced after last enrolled subject has completed follow-up 12 months after EoT (primary endpoint). The interim report will include analyses of the primary and some secondary endpoints based on data assembled for each enrolled subject up until the time point corresponding to 12 months after EoT. The assembled data will be locked and the study unblinded only for the statisticians. Main analysis for the primary endpoint will be done using the ITT population. Analysis on the PP population will be performed as sensitivity analysis. Subgroup analysis will be performed on ITT population for AMH change on these prospectively defined subgroups:

Age (14–19; 20–34; **≥**35)Ovarian reserve (AMH) at baseline (0.68–2.3; 2.4–4.9; **≥**5 (µg/L)).Cancer diagnosis (breast cancer, lymphoma, sarcoma and leukaemia)Type of cancer treatment (high risk, intermediate risk and low risk).Exposure to gonadotoxic cytostatics (corresponding to cumulative dose, mg CPA)/.

Analyses results and aggregated descriptive summaries will be disclosed to the sponsor.

At the end of study, after the extended follow-up period of 5 years, and once all study data for the mentioned visits are collected and verified in the eCRF system, the unblinding of all subjects will take place for investigators and sponsor. All available data will be used in the statistical analysis. A subject who withdraws prior to the last planned visit in the study will be included in the analyses up to the time of discontinuation. All efficacy and safety analyses will be performed at end of study when the study database is released for unblinding.

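### The fertility and childbirth objective is worded for women who attempt pregnancy, a group formed after randomisation, and does not match the ITT evaluation stated for secondary endpoints

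*Protocol article*

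**What the plan says.** The Hypothesis and aim section presents Table 2 as the complete list of objectives. Its single entry on fertility and births reads: "To investigate fertility and childbirth after cancer treatment in women with or without GnRHa who attempt pregnancy during follow-up". The neighbouring entries on amenorrhoea, ovarian insufficiency and survival carry no comparable restriction.

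The section on sample size and statistical analyses states: "Primary and secondary endpoints will be evaluated using the intention-to-treat (ITT) (ie, all randomised subjects"), followed by the per-protocol and safety sets. The article does not say how the attempter wording and this statement fit together.

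On earlier trials, the section on clinical studies of GnRHa says that "as all available studies have been unblinded, the women who received GnRHa have known that the drug was administered to protect their fertility potential", and that this potential bias has been discussed "as the women who received GnRHa also reported higher frequency of pregnancy attempts". Table 1 says of one earlier breast cancer trial: "Women attempted and achieved pregnancy to a higher degree in the group that received GnRHa".

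The Blinding section lists those kept blind: "All personnel involved in the study, sponsor, investigators, site staffs and monitors, statisticians and subjects, except personnel preparing triptorelin/placebo" at the local site and one unblinded monitor. Under the Data analysis plan, only statisticians are unblinded at the 12-month report. After the 5-year follow-up, "the unblinding of all subjects will take place for investigators and sponsor". Under Study interventions, reproductive outcomes are collected by questionnaire with no stated limit to attempters. The full list of secondary endpoints is in the supplement, which is not shown.

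**The concern.** Randomisation makes the arms comparable as randomised. It does not make comparable the subsets who later choose to try for a child. Several things that plausibly drive that choice are outcomes this trial studies by arm: resumption of menses, ovarian insufficiency, recurrence and disease-free survival. If GnRHa works as hypothesised, it may change which women feel able to try, and the attempters in the two arms may then differ in underlying fertility. A pregnancy rate per attempter could differ with no effect on the ability to conceive, or could hide a real effect.

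The trial's stated aim is preserved fertility. AMH is a marker of it, while pregnancy and birth are the direct outcomes, so this objective should be readable as a randomised comparison even though it is a non-key secondary one.

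**Working it through.** **Plan's own figure.** There is none for this objective. The only sample size is for AMH in the breast cancer cohort and has no bearing here. No attempt rate or pregnancy rate is given anywhere.

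**Reading the sections together.** Table 2 sets the population of the objective as attempters. The analysis section sets the population for secondary endpoints as everyone randomised. Both can be followed only if attempters are treated as a subset of the ITT set analysed by assigned arm. That is feasible, but it is then a subgroup defined by a post-randomisation event and not an ITT comparison.

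**When does restricting to attempters bias the comparison?** For each arm:

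pregnancy rate in all randomised = attempt rate × pregnancy rate per attempter.

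Illustration, with every rate an assumption. Half the women have good fertility (60% conceive if they try) and half poor (20%). The drug has no effect on conceiving once a woman tries. With attempt rates g (good) and p (poor):

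- attempt rate = 0.5g + 0.5p
- pregnancy per randomised woman = 0.5g × 0.6 + 0.5p × 0.2
- pregnancy per attempter = second line ÷ first line

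Results are placebo vs GnRHa:

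| Case | g/p placebo | g/p GnRHa | Attempt rate | Per attempter | Per randomised woman |
|---|---|---|---|---|---|
| (a) same attempts in both arms | 30/30% | 30/30% | 30% vs 30% | 40% vs 40% | 12% vs 12% |
| (b) all attempts rise equally on GnRHa | 30/30% | 40/40% | 30% vs 40% | 40% vs 40% | 12% vs 16% |
| (c1) more poor-fertility women try on GnRHa | 30/20% | 30/30% | 25% vs 30% | 44% vs 40% | 11% vs 12% |
| (c2) the same, more strongly | 30/15% | 30/30% | 22.5% vs 30% | 46.7% vs 40% | 10.5% vs 12% |
| (d) more good-fertility women try on GnRHa | 30/30% | 40/30% | 30% vs 35% | 40% vs 42.9% | 12% vs 15% |

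Worked line for (c1), placebo: attempts 0.15 + 0.10 = 0.25; pregnancies 0.15 × 0.6 + 0.10 × 0.2 = 0.11; 0.11 ÷ 0.25 = 44%.

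The attempter comparison is unbiased in (a) and (b). It shows a spurious deficit for GnRHa of 4 to 7 points in (c) and a spurious gain of about 3 points in (d). What matters is whether treatment changes the mix of women who try. The all-randomised figures differ in (b) to (d) solely because attempts differ, which can be seen only if the attempt rate is reported beside them.

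**The case against.** The strongest counter-case has four parts.

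1. *A reader might infer that the trial repeats the bias it criticises in earlier studies.* The documents do not support this. That bias is attributed to women knowing their allocation and attempting more often. Here participants and nearly all staff are blinded, and general unblinding follows the 5-year visit. Restricting to attempters partly answers unequal attempt rates, as case (b) shows. Participants might guess their allocation from drug effects, but that is an inference the article does not discuss.

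2. *A reader might also infer that fertility will be compared only among attempters.* The objective says investigate, names no test or endpoint, and the full endpoint list is not shown. An all-randomised endpoint may exist there. This part stands, and it limits the point to the wording of the objective.

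3. *Attempters can be analysed by assigned arm within the ITT set, so there is no outright contradiction.* This is fair. The sections are unreconciled rather than incompatible.

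4. *The all-randomised rate can mislead about fertility more than the attempter rate.* This is true in case (b): a 4-point gap per randomised woman against none per attempter. The all-randomised rate is a valid effect of assignment, but it mixes willingness to try with ability to conceive. With enrolment from age 14, many participants may not seek pregnancy within 5 years. Asking about those who do is a sensible question, so the attempter analysis should be kept.

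None of this restores the protection of randomisation to a comparison among attempters.

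**Conclusion.** The point holds in a limited form. The only listed fertility and childbirth objective is worded for a post-randomisation group that treatment may influence. A between-arm difference in that group cannot be read as a randomised effect, and the wording does not match the stated ITT evaluation of secondary endpoints.

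Bias requires that treatment changes who attempts. If it does not, there is none. The direction is unknown and the documents offer nothing from which to size it; the gaps shown above rest wholly on assumed rates and indicate only that either sign is possible. The primary AMH analysis is unaffected. As a non-key secondary objective its consequence is modest, but it is the one closest to the question of preserved fertility and the remedy is nearly free.

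**What to change.** Amend the objective and the matching analysis text so that three results are reported together:

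- Clinical pregnancy and live birth by 5 years after EoT, by assigned arm, in all randomised women, with breast and non-breast cohorts separate. State this as the effect of assignment.
- Pregnancy attempt by arm, as an outcome in its own right, so that a difference driven by attempts can be recognised. Similar attempt rates would be reassuring but would not prove that the same kinds of women tried.
- Pregnancy and live birth among attempters, kept as supportive and labelled non-randomised.

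If the full protocol already defines all-randomised endpoints, aligning the wording of Table 2 is enough.

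The cost is wording and one more analysis. The questionnaires already collect reproductive outcomes; check that they record attempts for every participant. The price in interpretation is an all-randomised rate diluted by women not seeking pregnancy, which must be read together with the attempt rates.
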